# Protect MSM from HIV and other sexually transmitted diseases by providing mobile health services of partner notification: protocol for a pragmatic stepped wedge cluster randomized controlled trial

**DOI:** 10.1186/s12889-020-09162-x

**Published:** 2020-07-14

**Keywords:** Stepped wedge cluster randomized controlled trial, Partner notification, Men who have sex with men, HIV incidence, Sexually transmitted disease, mHealth application

## Abstract

**Background:**

Recently, more and more men who have sex with men (MSM) look for casual partners through online dating platforms in China. However, most are unable to know their partners’ HIV and other sexually transmitted diseases (STD) statuses, leading to the rapid increase in HIV infection among Chinese MSM. Effective partner notification is urgently needed to increase the risk awareness of MSM and prevent HIV and other STDs transmission. However, the traditional intervention mainly targets to the HIV-positive MSM and the effect is not promising. Our study aims to provide Internet-based partner notification, along with a series of health services for HIV-negative MSM to protect them from HIV and other STDs.

**Methods:**

A pragmatic stepped wedge cluster randomized controlled trial design is used to evaluate the effectiveness of a new intervention paradigm, which aims to reduce HIV and other STDs incidences among MSM in China. Through integrating a mobile health (mHealth) service application (app) to the current HIV and other STDs prevention and control methods, the new paradigm provides partner notification of HIV, syphilis, hepatitis B, and hepatitis C statuses. A total of 6172 MSM in 16 districts of Beijing, China will be recruited and randomized to sequentially receive partner notification intervention through the app at 6-month intervals. The primary outcomes are HIV incidence and the additional cost of the intervention. The secondary outcomes include incidences of syphilis, hepatitis B, and hepatitis C, disease transmission social networks, testing adherence, knowledge of HIV and STDs control, health self-responsibility awareness, changes of high risk behaviors and other related outcomes. The generalized linear mixed models (GLMM) will be used to analyze the differences of outcomes in the control period and in the intervention period.

**Discussion:**

We expect that the HIV incidence will be significantly lower and the secondary outcomes will also be improved with providing health service of partner notification through mhealth intervention. The feasible and affordable public health intervention paradigm will have implications for HIV and STDs prevention and control among MSM and other key populations.

**Trial registration:**

ClinicalTrials.gov, NCT04349748. Registered on 16 April 2020.

## Background

The HIV/AIDS epidemic in China is developing rapidly in recent years, with the number of people living with HIV increasing from 0.44 million in 2011 to 0.95 million in 2019 [1, 2]. Men who have sex with men (MSM) are the major key population of HIV/AIDS. Male homosexual transmission has become the second major HIV transmission route in China only after heterosexual transmission, which accounts for about a quarter of the new HIV/AIDS cases [2, 3]. Having unprotected anal sex is the main risk of MSM to be infected, which is also associated with interrelated risk factors, such as non-persistent sexual partners, alcohol and drug use, and co-infection of other sexually transmitted diseases (STDs) [4–10].

With the development of the Internet and the popularity of mobile devices, the ways and venues of MSM seeking sexual partners had changed dramatically. A change from seeking sexual partners through offline venues, such as gay bars, baths and parks, to online ways through Internet or mobile applications (app) is witnessed in recent years [11–13]. The rise of online dating applications (ie, Blued, Grindr) in China tremendously reduces the cost and inconvenience for MSM to seek casual sexual partners [14–16]. Some MSM who sought sexual partners through the Internet do not know each other before, not to mention each other’s HIV infection status, which brings higher risk of HIV transmissions [17, 18]. In addition, the convenience of transportation increases the risk of cross-regional HIV transmission. All of these lead to greater difficulties in HIV prevention and control among MSM who sought sexual partners through Internet, as it is always difficult to find the sexual partner again afterwards. Recent research in China showed the HIV incidence among MSM online dating apps users was about four times higher than that of nonusers (8.5 per 100 person-years vs 2.0 per 100 person-years) [19]. Therefore, MSM’s behaviors of seeking sexual partners through Internet should be paid more attention. It is important for them to know their sexual partners’ real HIV status, strengthen the awareness of health self-responsibility and give each other the opportunity to make decisions on whether to meet and have sex.

Partner notification is a public health approach to prevent and control HIV infection among HIV high-risk subpopulations, especially MSM. It is recommended by the World Health Organization (WHO) and has been implemented in 67 countries around the world, including China [20]. Partner notification denotes that the sexual partners should take the initiative to tell each other their HIV infection statuses, especially those living with HIV/AIDS; it also encourages sexual partners to receive HIV testing [20]. Most existing methods of partner notification target to newly HIV-infected individuals’ sexual partners, for example, health workers may provide assisted HIV partner notification services on the condition that the newly HIV-infected individuals agree to, through personal telephone or address contact, e-postcards, and some website-based methods [21–23]. However, these methods aimed to offer HIV-infected individuals an opportunity to tell their sexual partners about their HIV statuses anonymously after sexual behaviors, which is a afterward remedy. Partners of the HIV-infected individuals are still at high risks. Meanwhile, some issues on the feasibility and effectiveness of these existing partner notification methods exist, including difficulties in daily implementation, low response rate, and high cost in time, human resources etc. [24, 25].

Seeing these problems, we developed a mobile health (mHealth) app for partner notification to encourage interactive queries among MSM before having sex, even before meeting. It targets not only to HIV-infected MSM, but HIV negative MSM as well. Through integrating the mHealth app to the current HIV and other STDs prevention and control methods, we set up a new and feasible public health intervention paradigm, to realize the goal of moving forward the intervention and reduce the HIV incidence among MSM.

This study has several objectives. First, we aim to evaluate the effect of the additional partner notification intervention in reducing HIV incidence among MSM. Second, the incremental cost of the added interventions based on existing HIV prevention measures is analyze, to evaluate whether it is cost-effective. Our third objective is to evaluate the effect of the additional partner notification intervention in some secondary outcomes, including syphilis and other sexually transmitted diseases incidence, HIV and related diseases transmission among social networks, HIV testing adherence, knowledge and health self-responsibility awareness, changes of sexual behaviors, etc. We hypothesize that the intervention services are effective and cost-efficient.

## Methods/design

### Study design and timeline

This research will use a stepped wedge cluster randomized controlled trial (SW-CRCT) design. It is commonly used to evaluate service delivery or policy interventions of clusters [26]. This research will be implemented in Beijing, whose sixteen districts are defined as the clusters. We assign the sixteen districts into four research groups using stratified randomization, with four districts in one group. The open cohort SW-CRCT will last 2.5 years, which is anticipated to be conducted from July, 2020 to December, 2022. Five continuous observational periods at a 6-month interval are divided. According to the standard design of SW-CRCT, in the first 6-month “the initial period”, no group is exposed to the additional partner notification intervention. After that, the four groups begin to cross from the control condition to receive the partner notification intervention sequentially at 6-month intervals. Once one group receives the partner notification intervention, the intervention will continue until the end of the research. And at the last 6-month period, all of the four groups will receive the additional partner notification intervention. (Fig. 1).

**Fig. 1 Fig1:**
[figure not shown]
Stepped wedge design of the intervention implementation

There are several reasons for such a SW-CRCT design. Firstly, the implementation of partner notification needs communication and interaction among MSM, which can only be achieved through the accumulation of a larger number of participants at the cluster (district) level after the recruitment period. Therefore, the intervention needs to be applied to cluster-level instead of individual-level, and cluster randomization is used instead of individual randomization. Secondly, SW-CRCT design is a pragmatic design that is increasingly used worldwide in recent years. This design allows to evaluate the effect of intervention in a real-world condition considering the social environment and logistical issues, which aligns with our aims [26, 27]. Thirdly, the SW-CRCT design ensures that all clusters and participants receive the partner notification intervention, which is more ethical considering the partner notification and other interventions we implement may not bring obvious harm to our participants [26, 28].

### Study setting and recruitment

We will conduct our research in Beijing, the capital city of China with high population mobility and demographic heterogeneity and high burden of HIV and related STDs among MSM. We will cooperate with a local community-based organization (CBO) named *Man Wellness Center* to recruit participants and provide HIV and other STDs (syphilis, hepatitis B, and hepatitis C) testing services. *Man Wellness Center* is one of the largest and most popular CBO for MSM to give them HIV and STDs prevention and medical services.

Participants will be recruited in two ways: offline and online. The offline recruitment will be implemented in offline venues, such as the clinic sites of the CBO for routine work, and the gay bars, bathrooms, parks for outreach services. The online recruitment will be implemented through online platforms, such as WeChat, QQ, Weibo and Blued. The process of recruitment includes four steps: (1) Determine whether the participant recruited meets the eligibility criteria. (2) Introduce the research and tools for interventions (the app and the WeChat official account) if eligible. (3) Help the participant sign the electronic informed consent through the app and then show him the functions of the app and WeChat official account. The content of the electronic informed consent contains all necessary information as traditional paper version of informed consent, and the signed electronic informed consent will be stored in the database. Participants under the age of 18 are asked to register the app system and sign the consent accompanied by a guardian, and written consent is also obtained from the guardian. (4) Invite the participant to fill in the baseline questionnaire through the app. (5) Provide HIV and other STDs testing services and upload the test results through the backend database. The recruitment will start from the beginning of the research, and we will stop recruitment in the last 6 months of the research. If the participant has HIV and other STDs testing during the follow-up period, he will be invited to finish a follow-up questionnaire.

If the participant is recruited offline, to protect the participants’ privacy and confidentiality, the process of the recruitment will be implemented one-to-one by the CBO’s trained staff in a private environment. If the participant is recruited online, the process will also be implemented one-to-one through online platforms. After finishing the baseline questionnaire, the participant will be suggested to use the HIV and STDs self-testing services or go to the CBO clinics to receive facility-based testing. If the online recruited participant does not conduct the testing 1 month after registering, he will receive testing reminding information through the app and mobile phone short message.

Ethical Approval for this study has been obtained from the Peking University Institutional Review Board (IRB00001052–16016).

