#### Intervention implementation

Based on the CBO’s existing HIV and STD prevention methods, such as HIV and STDs testing services, we construct a new integrated intervention model for HIV and STDs control among MSM by adding two parts of interventions.

The first part is to strength MSM’s safety awareness of seeking sexual partners and sense of health self-responsibility. Two measures will be implemented as follows: (1) Provide health education materials weekly to participants through the WeChat official account and app’s health education module. These materials contain the harmfulness of HIV/AIDS and STDs, symptoms and signs of HIV/AIDS and STDs, awareness of receiving HIV and STDs testing on their own initiative, awareness of partner notification, HIV/AIDS and STDs prevention skills, related laws, related drug use instruction, and the harmfulness of drug abuse and its prevention. The content of health education will repeat every 6 months in order to ensure all participants receive the whole education content. (2) Provide HIV and STDs testing prompting service to HIV negative participants monthly according their test records individually through app’s prompt and warning module and mobile phone short messages.

The second part is to promote and encourage partner notification through the app. We expect if two MSM are dating through some online dating platforms, the partner notification and related warnings provided via the app will in a timely manner help them know each other’s HIV and STDs status before they are going to meet and have sex.

This research is designed as a pragmatic SW-CRCT study. The interventions participants received in the control period and the intervention period are different. In control period, they will receive health education through the WeChat official account and app, as well as HIV and STDs testing prompting service. The app’s test result self-query module is also opened to them to promote the use of the app and avoid the loss to follow-up. But the partner notification is not available. In intervention period, all interventions in the control period will continue, and the partner notification functions will be opened. (Fig. 1).

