### HIV and STDs testing

HIV and STDs testing will be conducted at baseline investigation during participants recruitment, and follow-up investigations by CBO staffs. There are two alternative ways that participants can receive testing services, including the “Mailing rapid test reagent kit” self-testing service and the facility-based testing service.

The “Mailing rapid test reagent kit” self-testing service bases on participants’ applications on the WeChat official account. The procedures for one participant applying for HIV and STD self-testing are as followed: (1) Fill in phone number and address information used to mail the test kit through the WeChat official account; (2) The CBO will send a package of rapid test reagent kit to the user (the kit is free of charge, but the express fee charged by express company is required); (3) Complete the self-testing using the test kit by himself. If he does not know how to use, he can see a teaching video provided on the WeChat official account; (4) Take a clear picture of the test reagent kit and upload it to CBO through the system; (5) CBO’s trained staff will check the results and generate a testing report for the user showing the result “Negative” or “Positive” of HIV and STDs and the date of this testing service. (Fig. 4).

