The second outcomes of this research include: (1) Positive seroconversion rate (incidence) of syphilis, hepatitis B, and hepatitis C. These indicators are calculated separately as the number of syphilis/hepatitis B/hepatitis C seroconversions divided by the total number of person-years. (2) HIV and related STDs transmission among social networks. Based on the partner notification information, we will construct the transmission networks of HIV and other STDs (syphilis, hepatitis B, and hepatitis C) among participants, and analyze the characteristics of these networks and factors associated with transmission of these diseases. (3) Testing adherence. This indicator is calculated as the proportion of participants whose every adjacent testing interval is no more than 3 months as recommended by China CDC. (4) Additional cost for finding per seroconversion. This indicator is calculated through the total additional cost of the integrated intervention model based on the existing HIV prevention measures provided as before divided by the total number of the HIV and STDs seroconversions. (5) Frequency of utilization for each intervention/service. This indicator is calculated through the total and average frequency of utilization for each intervention/service, such as health education, partner notification, HIV and STDs testing and so on. (6) Satisfaction of the interventions and services, measured through the follow-up questionnaires by the degree of satisfaction for participants of HIV and STDs testing service, health education, partner notification and other app’s functions. (7) Knowledge of HIV and related STDs. This indicator is measured by the baseline and follow-up questionnaires. The score of knowledge questions in the questionnaires will be used to represent participants’ level of knowledge. (8) Health self-responsibility awareness, including attitudes of HIV and STDs testing, safe sexual behaviors and partner notification. The attitudes are collected by questions in the baseline and follow-up questionnaires. (9) Sexual behaviors. They are measured through questionnaires, including questions about the number of different kinds of sexual partners, frequency of anal sex, condom use, and partner notification implementation. (10) Substance use behaviors. This indicator is measured by questionnaires about participants’ usage of methamphetamine, heroin, ecstasy, and some other sex-promoting drugs. (11) Psychological status. Self-rating anxiety scale (SAS) and Self-rating depression scale (SDS) are used to measure participants’ psychological status through questionnaires. (12) Referral rate of HIV and related STDs. This indicator is calculated as the proportion of new HIV and STDs infections who have received treatment. (Additional file 2).

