In this research, we create a feasible and affordable public health intervention paradigm, based on the existing HIV and STDs control methods. We integrate health education to strengthen their safety awareness and health self-responsibility, HIV and STDs testing prompting service and partner notification through app platform. To promote the convenience and privacy of HIV and STDs testing, we innovatively adopt multiple forms of testing service including the newly online HIV self-testing method “Mailing rapid test reagent kit” and the facility-based service. It can give participants more choices and may improve the adherence of the research. In this research, the SW-CRCT design is used for ethical and logistical concerns, which can minimize bias and make sure all participants receive the partner notification intervention. We expect our partner notification intervention can reduce the incidence of HIV and other related STDs, and it is cost-effective to be widely popularized in HIV and STDs control activities. It may also improve MSM’s knowledge, health self-responsibility awareness of HIV and STDs prevention, and testing adherence, as well as to reduce high risk behaviors. Based on the partner notification records we collect through the app, an innovative social network analysis will be conducted. The networks formed by the real partner notification connections are more objective and comprehensive than the connections found by traditional observational or cohort studies. The characteristics of the social networks can provide more guidance for HIV and STDs control among MSM.

One limitation of this research is that even though the interventions based on Internet and mobile phone app can be easily accepted by youth participants, some elderly people might feel it difficult to use. But it is worth noting that recent researches have showed that the age of recruited MSM is mainly 25 to 40 years old.

Our research is the first study to conduct Internet- and app-based integrated partner notification intervention in a large simple size, and will generate important research and policy implications for HIV and STDs control among MSM.

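### The follow-up questionnaire is tied to having a test, so five secondary outcomes, and satisfaction in part, are observed in men and at times selected by a behaviour the intervention is expected to change.

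*Protocol article*

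**What the plan says.** All references are to the protocol article.

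- **Trigger.** Study setting and recruitment: "If the participant has HIV and other STDs testing during the follow-up period, he will be invited to finish a follow-up questionnaire". The baseline form is handled differently. It is part of enrolment and is delivered electronically: "Invite the participant to fill in the baseline questionnaire through the app".
- **What counts as a test.** HIV and STDs testing: "There are two alternative ways that participants can receive testing services", namely a mailed self-test kit or a visit to a clinic site. Either one meets the trigger.
- **Outcomes that use the questionnaire.** The Outcomes section lists twelve secondary outcomes. Items 6 to 11 come from questionnaires; for knowledge, for example, "This indicator is measured by the baseline and follow-up questionnaires".
- **Testing as an outcome.** Item 3 concerns how regularly men test: "This indicator is calculated as the proportion of participants whose every adjacent testing interval is no more than 3 months as recommended by China CDC". The third objective in the Background names effects on "HIV testing adherence, knowledge and health self-responsibility awareness, changes of sexual behaviors, etc". The Discussion gives the expected direction: "It may also improve MSM’s knowledge, health self-responsibility awareness of HIV and STDs prevention, and testing adherence, as well as to reduce high risk behaviors".
- **Control condition.** Intervention implementation: "In control period, they will receive health education through the WeChat official account and app, as well as HIV and STDs testing prompting service". Partner notification is the component added in the intervention period.
- **Analysis.** Primary and secondary outcomes are compared between control and intervention periods in a mixed model, with intervention status and time as fixed effects and district and individual as random effects. Missing data are handled by the percentage missing per variable.

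**The concern.** A questionnaire outcome compared between conditions should be sought from the same kind of man, at the same kind of moment, in both. Here the occasion for asking is a test, and testing may respond to the intervention. If partner notification brings in men who would not otherwise have tested, or changes why and when men test, the people and moments sampled differ by condition. A change in who answers can then look like a change in behaviour, knowledge or mood, or can hide a real one.

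An analysis plan cannot fully repair this, because answers that were never requested cannot be recovered. There is also no defined denominator: without a scheduled form, a man who does not test has no questionnaire that is due, so it is unclear what percentage missing the missing-data rule would act on.

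**Working it through.** The article states no testing rate and no expected questionnaire response, so there is no figure of its own to reproduce on this point. The sample size concerns HIV incidence and does not bear on it.

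**1. Which outcomes are affected.** Items 6 to 11 are questionnaire-based: satisfaction, knowledge, self-responsibility awareness, sexual behaviours, substance use and psychological status. Items 7 to 11, five in all, can be contrasted between conditions. Satisfaction fits only in part: partner notification cannot be rated while it is closed, and satisfaction with testing is properly asked of men who tested.

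**2. Whether testing can differ by condition.** Education, testing prompts and result self-query run in both conditions, so any difference must come from partner notification. The article gives a plausible route: the module shows a partner the date and result of a man's recent test, which is a reason to hold a recent one. The authors also expect testing adherence to improve. This makes differential selection plausible, not established.

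**3. Size in an unadjusted comparison of respondents.** All rates here are assumptions. Let half the men be high-risk, with testing probability tH per period for high-risk and tL for low-risk men. The high-risk share of respondents is tH / (tH + tL).

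| Assumed testing | High-risk share | Shift from control |
|---|---|---|
| Control: 60% high-risk, 40% low-risk | 0.60/1.00 = 60.0% | – |
| Intervention, no change | 60.0% | 0 |
| Proportional rise: 75%, 50% | 0.75/1.25 = 60.0% | 0 |
| Rise in high-risk men only: 75%, 40% | 0.75/1.15 = 65.2% | +5.2 points |
| Rise in low-risk men only: 60%, 50% | 0.60/1.10 = 54.5% | −5.5 points |

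The shift in a reported behaviour is the shift in share times the difference in prevalence between the two types. With prevalences of 95% and 5% it is 5.2 × 0.90 = 4.7 points; with 80% and 20% it is 5.2 × 0.60 = 3.1 points.

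The same effect can be put as a risk ratio. Let testing rise from c to i, with prevalence a in men who test anyway and m in men who test only because of the intervention. With no true effect, RR = [c·a + (i − c)·m] / (i·a).

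- c = 0.5, i = 0.6, a = 0.4, m = 0.5: 0.25/0.24 = 1.04
- c = 0.5, i = 0.6, a = 0.4, m = 0.6: 0.26/0.24 = 1.08
- c = 0.5, i = 0.7, a = 0.4, m = 0.6: 0.32/0.28 = 1.14
- i = c: 1.00

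**4. What the planned model removes.** In a small simulation with no true effect, only high-risk men tested more (60% to 75%; low-risk 40% throughout). It used 4320 men, five periods, a baseline answer and a linear mixed model with a person intercept, with 5 replicates per setting.

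| Prevalence, high-risk / low-risk | Bias, respondents adjusted for time only | Bias, mixed model |
|---|---|---|
| 95% / 5% | about 4.5 points | about 0.5 |
| 80% / 20% | about 3.0 points | about 1.2 |

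With so few replicates these are indicative only. The person effect removes most of the bias when behaviour closely follows a stable type, and less when it does not.

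**5. What the model cannot remove.** The simulation selects on a fixed trait only. A person intercept is constant over time. If a man tests after a risky episode in control periods and more as routine in intervention periods, his answers refer to different moments, and a constant intercept does not adjust for that. A man with no follow-up form contributes no follow-up answer under any model.

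**The case against.** The strongest reply has four parts.

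**The trigger may not be exclusive.** The sentence gives one occasion and does not say it is the sole one. The testing section mentions follow-up investigations, and the Outcomes section points to an additional file that is not shown. A reader might infer that men who stop testing are never asked and that frequent testers are asked many times. The text supports neither as fact: it excludes no other route and gives no frequency. What stands is that the one stated rule depends on testing, and that the follow-up investigations appear only as testing occasions, without a timetable.

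**The planned model includes individuals.** This is correct and matters. A reader might take the 5-point shift in the high-risk share as the expected bias, but that is an unadjusted shift in respondent mix. For selection on stable traits, the planned model with baseline data would leave less.

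**Selection may not differ by condition.** Prompts run in both conditions, and men enter only if willing to test continuously. A proportional rise in testing gives no bias, and a rise concentrated in low-risk men reverses the sign. This stands: differential selection is a possibility built into the plan, not a demonstrated result.

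**The missing-data rule provides for investigating the mechanism above 20% missing.** It does, but it does not say when a form counts as missing for a man who did not test, and an investigation cannot supply his answers.

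**Conclusion.** The point holds as a weakness of data collection for five secondary outcomes and part of a sixth. It rests on two things in the article: the only stated trigger for the follow-up form is a test, and testing is an outcome expected to improve. It also assumes that no scheduled questionnaire exists in material not shown.

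Size and direction are unknown. Bias is zero if testing does not change or rises in proportion across risk groups. Under the assumed unequal changes it is about 3 to 5 points in an unadjusted comparison and about 0.5 to 1.2 points after the person effect, where selection is on a stable trait. Selection on when a man tests comes on top and was not quantified.

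Two stronger readings should be resisted. One is that half of the secondary outcomes are invalid between-condition comparisons: six of twelve are questionnaire-based, but satisfaction is only partly such a contrast, and bias is possible, not certain. The other is that the primary result is affected: HIV incidence does not come from the questionnaire, and nothing here bears on it.

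**What to change.** In the section on study setting and recruitment, replace the test-dependent invitation with a scheduled one. Send the follow-up questionnaire through the app to every enrolled man at the end of each 6-month period, whether or not he has tested, and add a questionnaire reminder to the app and text-message channels, which now carry testing reminders. Name this fixed-time form as the source of the analysed questionnaire outcomes, keep test-triggered forms as supplementary, and report response by condition and period.

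The cost is a scheduled push in an app that already delivers the baseline form, and a small added burden on respondents, who must be willing to complete the questionnaire to be eligible. Recruitment had not begun when the article was written, so the change could have been made before any data were collected.

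The change does not remove all selection. Men who use the app more may answer more, and opening partner notification may change app use. It does give a defined denominator that does not depend on testing, so non-response can be counted and examined by condition.
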